## Abstract

**Background:**

Insomnia and depression represent prevalent issues during adolescence. Auricular acupressure (AA), a simple, low-cost traditional Chinese medicine therapy with minimal adverse effects, has demonstrated efficacy in improving sleep quality and alleviating depressive symptoms in adult populations. However, existing research has predominantly focused on adults, with limited evidence regarding AA’s effectiveness in improving sleep and preventing depression among adolescents.

**Methods:**

This study is a single-center, double-blind, randomized controlled trial conducted in Nanjing, China. Participants are students from junior and senior high schools in Nanjing. A multi-stage stratified cluster sampling method is used to recruit students from 7th and 8th grades (junior high) and 10th and 11th grades (senior high). Baseline data will be collected using the Chinese version of the Pittsburgh Sleep Quality Index (PSQI), Beck Depression Inventory (BDI), Adolescent Sleep Hygiene Scale (ASHS), Children’s Depression Inventory (CDI), Adolescent Self-rating Life Events Checklist (ASLEC) and Adolescent Sleep-Wake Scale (ASWS), and insomnia patients will be identified. Adolescents who met the inclusion and exclusion criteria and whose guardians signed informed consent forms will be enrolled in the study. They will be randomly assigned to one of three groups: AA group, sham auricular acupressure (SAA) group, and control group. The treatment lasted for 8 weeks, with follow-up assessments at 3 and 6 months post-treatment. The primary outcome measures are PSQI and BDI scores, while secondary outcome measures included ASHS, CDI, ASLEC, and ASWS scores.

**Discussion:**

This prospective study evaluates AA’s efficacy in enhancing sleep quality and preventing depression in adolescents. The findings will elucidate AA’s potential clinical applications for adolescent insomnia treatment and depression prevention, thereby providing evidence to support its broader implementation in this population.

**Clinical trial registration:**

http://itmctr.ccebtcm.org.cn/, identifier ITMCTR2024000343.

## Introduction

1

Depression is one of the most common mental disorders, characterized primarily by persistent and significant low mood. Adolescence is a critical period for the onset of depression. Research shows that the incidence of depression rises sharply after puberty, with the prevalence of depression in children being less than 1%, while in adolescence it increases to more than 4%–5% (1). Recent studies indicate that the prevalence of mild to moderate depression among adolescents is as high as 20% (2). Most cases remain undiagnosed or untreated, thereby increasing the risk of suicide in adolescents (3).

Insomnia is closely related to depression, and in both the DSM-IV and the latest DSM-V diagnostic criteria (4, 5), insomnia symptoms are listed as core symptoms of depression. Furthermore, many symptoms of daytime functional impairment in the diagnosis of insomnia overlap with the clinical manifestations of depression, such as lack of energy or fatigue, mood swings, and somatic symptoms. This overlap in diagnostic criteria further suggests that insomnia and depression share significant clinical similarities. Increasing evidence indicates that insomnia is not only a symptom of depression but may also be a potential predictive factor for depression (6).

Adolescence represents a critical developmental period characterized by significant alterations in sleep behavior. During this phase, adolescents experience physiological changes including delayed circadian rhythms and diminished homeostatic sleep regulation (7), culminating in a “perfect storm” of sleep disturbances manifested as delayed sleep onset, insufficient sleep duration, and difficulties in sleep maintenance (8). At the physiological level, the delayed maturation of the suprachiasmatic nucleus results in circadian phase delay, coupled with impaired homeostatic regulation of sleep need, leading to prolonged wakefulness in adolescents (8). Concurrently, psychosocial factors such as academic stress, social demands, and blue light exposure from electronic devices further disrupt sleep-wake cycles (9). Epidemiological studies have confirmed that sleep problems in adolescents significantly increase depression risk (10, 11), with this association being validated by a prospective cohort study in Guangzhou, China, demonstrating a dose-response relationship between reduced sleep duration (AOR=0.86, 95%CI: 0.80–0.92) and poorer sleep quality with subsequent depressive symptoms (12). Notably, while a bidirectional relationship exists between insomnia and depression (13), longitudinal studies more frequently indicate that insomnia precedes depressive onset, with some cases traceable to the perinatal period (14). Neurobiological research further reveals that decreased N3 sleep and diminished delta power during adolescent brain reorganization (15) may impair functional connectivity in emotion-regulation neural circuits (e.g., prefrontal-amygdala pathways), thereby establishing the neurobiological basis for insomnia-depression progression. Collectively, this evidence underscores the crucial need to develop adolescent-specific insomnia interventions for depression prevention.

Auricular acupressure (AA) is a non-pharmacological therapy originating from China, widely used for treating insomnia and depression. With historical roots tracing back to the Huangdi Neijing and systematically developed into modern auricular therapy by French physician Paul Nogier in the 1950s (16), AA primarily employs magnetic beads or Vaccaria seeds to stimulate specific auricular points for physiological regulation. The auricle represents the only somatic region with direct vagus nerve distribution, providing a neuroanatomical foundation for AA’s mechanism of action. By stimulating auricular vagal branches, AA transmits neural signals to brain regions critically involved in depression and insomnia, including the solitary nucleus, dorsal raphe nucleus, hippocampus, and prefrontal cortex (17–19). This intervention not only enhances cerebral hemodynamics and increases regional blood flow (20) but also modulates the secretion of sleep-related hormones and neurotransmitters such as serotonin, γ-aminobutyric acid, and melatonin (21), thereby improving sleep quality. Clinical studies demonstrate AA’s efficacy in enhancing sleep efficiency, reducing sleep latency, prolonging total sleep time, and alleviating comorbid anxiety and depressive symptoms (22).

Notably, while AA has shown robust therapeutic effects in adult populations, high-quality studies focusing on adolescents remain scarce, particularly regarding prospective prevention of adolescent depression. Furthermore, conventional first-line treatments like cognitive behavioral therapy face implementation challenges in school settings due to time constraints and operational complexity. In contrast, AA offers distinct advantages including technical simplicity, minimal adverse effects (23), and suitability for group administration, making it particularly amenable for school-based interventions. These characteristics warrant further systematic investigation of AA’s potential in adolescent mental health management.

Based on this, we have designed a randomized controlled study to screen adolescent insomnia patients using a multi-stage stratified cluster sampling method and randomly assign them to three groups: AA group, sham auricular acupressur (SAA) group, and control group. The intervention lasts for 8 weeks, and follow-up will be conducted at 3 months and 6 months post-treatment to evaluate the therapeutic effects of AA on adolescent insomnia and its potential to prevent depression. This study aims to explore a simple, safe, and effective intervention method, providing scientific evidence for the prevention of adolescent depression.

## Materials and methods

2

### Study design

2.1

This study is a randomized controlled trial aimed at observing the efficacy of AA in treating insomnia and preventing depression in adolescents. The study protocol adheres to the SPIRIT guidelines. The study is conducted in Nanjing, and the participants are students from junior and senior high schools in Nanjing. A multi-stage stratified cluster sampling method is used to select students from the first and second grades of junior high school, and the first and second grades of senior high school. Adolescents with insomnia are identified and randomly assigned to three groups: AA group, SAA group, and control group. Adolescents with insomnia are diagnosed according to the third edition of the International Classification of Sleep Disorders (ICSD-3). Students who meet the inclusion criteria, along with their legal guardians, will be provided with an informed consent form. Students who agree to participate will be included in the study. The study flowchart is shown in **Figure 1**, and the timeline is shown in **Figure 2**.

**Figure 1 f1:**
[figure not shown]
Flow diagram of the trial.

**Figure 2 f2:**
[figure not shown]
Schedule of enrolment, interventions, and assessments.

### Participants

2.2

This study is conducted in Nanjing, and the participants are students from junior and senior high schools in Nanjing. The study employed a multi-stage stratified cluster sampling approach, with the sampling process divided into three stages: educational level stratification, school stratification, and class sampling. First, schools were stratified by educational level into junior high school groups (grades 7 and 8) and senior high school groups (grades 10 and 11), excluding graduation classes (grades 9 and 12) to avoid potential interference from academic transitions on follow-up studies. Second, during school sampling, a stratified random sampling approach was adopted where junior and senior high schools were further substratified by geographic location (district, street/town) and school size (categorized into <800 students and ≥800 students based on enrollment numbers), ensuring proportional representation of each stratum relative to the overall population. Subsequently, four schools were independently and randomly selected from each stratum within both junior and senior high school groups. Finally, during class sampling, one target grade was randomly selected from grades 7 or 8 in junior high schools and grades 10 or 11 in senior high schools across the four sampled schools. For combined junior-senior high schools, their junior and senior sections were separately categorized into corresponding groups for independent sampling participation. In cases where a school had only one class in the target grade, that class was automatically included with documentation of this circumstance. Throughout the sampling process, detailed records of each school’s stratification attributes were maintained, and randomness in class selection was rigorously ensured.

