### Randomization

2.5

After screening based on the inclusion and exclusion criteria, eligible adolescent insomnia patients will be randomly assigned in a 1:1:1 ratio to the AA group, SAA group, or control group. The randomization sequence will be generated by researchers who are not involved in the trial implementation or statistical analysis using SPSS 25.0 software. The sequence will be hidden using the envelope method, and each envelope will contain the randomization order for patient allocation. A designated person will be responsible for patient inclusion, and patients will receive the corresponding envelope in the order of enrollment.

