### Statistical analysis

2.9

Statistical analyses will be performed using SPSS 25.0 (SPSS, Chicago, IL, USA). The incidence of adolescent depression will be calculated based on the Beck Depression Inventory (BDI) thresholds established in prior studies. Continuous variables will be presented as mean ± standard deviation, while categorical data will be expressed as percentages or proportions. A p-value <0.05 will be considered statistically significant for intergroup differences, and p<0.01 will indicate highly significant differences.

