#### Intergroup comparison methods

2.9.1

For normally distributed measurement data meeting the assumptions of parametric tests, within-group pre- and post-treatment comparisons will be conducted using paired-sample t-tests. Intergroup comparisons will employ one-way ANOVA. Non-normally distributed measurement data will be analyzed using nonparametric rank-sum tests, and categorical data will be assessed via chi-square tests or Fisher’s exact probability test. These comparisons will evaluate the therapeutic effects of auricular acupressure.

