#### Multi-timepoint data analysis

2.9.2

For repeated-measures data satisfying the sphericity assumption, repeated-measures ANOVA will be applied. If the sphericity assumption is violated, Greenhouse-Geisser correction or multivariate ANOVA will be used. This analysis will examine the main effect of time on outcome measures and potential time-by-group interactions.

For non-normally distributed data or datasets with significant missing values across timepoints, mixed-effects models will be employed. These models accommodate unbalanced data and missing values while accounting for intra-individual correlations.

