#### Correlation analysis and regression modeling

2.9.4

Independent t-tests and chi-square tests will identify significant associations (p<0.05) between depression and demographic features, sleep patterns, or life events. Significant factors will be incorporated into binary logistic regression models to evaluate their relationship with adolescent depression.

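### The depression risk-factor analysis (section 2.9.4) ignores the clustering of pupils by school, so standard errors for factors that vary mainly between schools would be too small

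*Protocol article*

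**What the plan says.** **Sampling (section 2.2).** "The study employed a multi-stage stratified cluster sampling approach". Within the strata, "four schools were independently and randomly selected from each stratum within both junior and senior high school groups". One target grade is then drawn, and classes are sampled. School attributes are to be recorded.

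**Allocation (section 2.5).** "eligible adolescent insomnia patients will be randomly assigned in a 1:1:1 ratio to the AA group, SAA group, or control group". The unit of randomisation is the pupil, not the school or class.

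**Risk-factor analysis (section 2.9.4).** Independent t-tests and chi-square tests look for associations of depression with demographic features, sleep patterns and life events. Those with p<0.05 go forward: "Significant factors will be incorporated into binary logistic regression models to evaluate their relationship with adolescent depression". The section does not say whether it uses the randomised pupils or the larger screened group.

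**Other analyses.** In section 2.9.1, "Intergroup comparisons will employ one-way ANOVA". In section 2.9.2, mixed models are a fallback, described as "while accounting for intra-individual correlations". In section 2.9, "The incidence of adolescent depression will be calculated based on the Beck Depression Inventory (BDI) thresholds established in prior studies"; no standard error or confidence interval for that incidence is described.

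No stated method mentions school, class, a cluster-robust variance or a design effect.

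**The concern.** Pupils in one school share teachers, workload, timetable and neighbourhood, so their depression status is likely to be correlated. Tests that treat them as independent credit the data with more information than they hold. The loss is greatest for a characteristic that is constant within a school, because the real sample size for it is then close to the number of schools.

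Some plausible demographic features are of this kind by design. Educational stage is a sampling stratum. Because one grade is drawn, grade is fixed within a school's junior or senior section. Age follows grade closely. These factors are not randomised, so the allocation gives them no protection.

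The error enters twice: at the p<0.05 screen, which decides what reaches the model, and again in the standard errors of the model. At stake is a spurious claim that, say, senior-high or older pupils are at different risk of depression.

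**Working it through.** **Inputs from the article (section 2.3).** 52/(1 − 0.20) = 65 per arm; 3 × 65 = 195 randomised; 195/0.20 = 975 screened. These three steps reproduce. The article gives no figure on clustering to reproduce.

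**Assumptions.** The ICC is not given; 0.01 to 0.05 is used, with 0.10 as an extra value in the simulation. The total number of schools is not given either. Four schools in each of two educational levels makes 8; further strata would make more, so 16 and 32 are shown as well.

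**Formulas for a factor constant within school.** With K schools and m = 195/K:
- design effect DE = 1 + (m − 1) × ICC
- ratio of true to unadjusted standard error = √DE
- true error of a nominal 5% test = 2 × [1 − Φ(1.96/√DE)]

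Example for K = 8: m = 24.4. At ICC 0.05, DE = 1 + 23.4 × 0.05 = 2.17, √DE = 1.47, 1.96/1.47 = 1.33, and the true error is 18.3%.

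| Schools | m | DE at ICC 0.01 / 0.02 / 0.05 | SE ratio | True error |
|---|---|---|---|---|
| 8 | 24.4 | 1.23 / 1.47 / 2.17 | 1.11 / 1.21 / 1.47 | 7.8% / 10.6% / 18.3% |
| 16 | 12.2 | 1.11 / 1.22 / 1.56 | 1.05 / 1.11 / 1.25 | 6.3% / 7.6% / 11.7% |
| 32 | 6.1 | 1.05 / 1.10 / 1.25 | 1.03 / 1.05 / 1.12 | 5.6% / 6.2% / 8.0% |

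**Simulation check.** 8 schools, 20% depressed (an assumption, taken from the prevalence in the Introduction), ICC on the logit scale, 1,500 runs per setting, no true effects. The entries are the type I error of unadjusted tests, except the last row.

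| Quantity | 195 pupils, ICC 0.02 / 0.05 / 0.10 | 975 pupils, ICC 0.02 / 0.05 / 0.10 |
|---|---|---|
| Logistic, school-level factor | 0.08 / 0.11 / 0.19 | 0.20 / 0.37 / 0.47 |
| Logistic, pupil-level factor, no clustering | 0.05 / 0.06 / 0.05 | 0.04 / 0.05 / 0.04 |
| Logistic, pupil-level factor with its own ICC of 0.10 | 0.04 / 0.06 / 0.06 | 0.07 / 0.08 / 0.11 |
| Between-arm chi-square or ANOVA | 0.04 to 0.06 | 0.04 to 0.06 |
| SE of overall proportion depressed, true/unadjusted | 1.11 / 1.30 / 1.52 | 1.52 / 2.09 / 2.86 |

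The Monte Carlo standard error at 5% is √(0.05 × 0.95/1500) = 0.006, so 0.04 to 0.06 cannot be told from nominal.

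Formula and simulation differ mainly because of the ICC scale. At 20% prevalence, a logit-scale ICC of 0.05 means a school variance of (0.05/0.95) × 3.29 = 0.173, or about 0.173 × 0.16 = 0.028 as an ICC on the proportion scale. Then DE = 1 + 23.4 × 0.028 = 1.65 and √DE = 1.29, which matches the simulated 1.30.

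**Arm contrast.** With individual randomisation, omitting school leaves between-school variance in the residual. The standard error is overstated by 1/√(1 − ICC): 1.005 at ICC 0.01 and 1.026 at ICC 0.05.

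**The case against.** **The trial's own question is untouched.** This stands. A reader might infer from cluster sampling that the PSQI and BDI comparisons are invalid, or that the sample size needs a design effect. Neither follows: pupils are allocated individually, and the between-arm tests keep their nominal error in the simulation. Omitting school there is slightly conservative.

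**Most factors in section 2.9.4 are measured per pupil.** This also stands. A reader might infer that every risk-factor p-value is too optimistic. At 195 pupils, unadjusted tests of sleep patterns and life events stay at about 4% to 6%, even when the factor itself clusters with an ICC of 0.10. Educational stage and grade are also not named in the section; they are plausible demographic features, and age is listed as a baseline characteristic in section 2.9.3.

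**No interval for incidence is planned.** Correct. One cannot say that the plan reports too narrow an interval, only that any interval reported for overall incidence would need the adjustment.

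**The size leans on assumptions.** This stands too. Eight schools is a low count, the formula ignores any gain from stratifying by location and school size, and the logit-scale simulation gives smaller figures at the same nominal ICC.

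**Random-effect structure may be left to an unseen analysis plan.** This holds for section 2.9.2, whose wording on within-person correlation does not exclude other random effects. It is weaker for section 2.9.4, where the article fixes the tests, the entry threshold and the model, and all of them assume independent pupils.

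**Conclusion.** The concern holds for one secondary analysis and one kind of factor. In section 2.9.4, associations of depression with factors that vary mainly between schools would be tested with standard errors that are too small. With 8 schools, 195 pupils and an ICC of 0.01 to 0.05, the true error of a 5% test is about 8% to 18% by formula, and about 8% to 11% by simulation at a logit-scale ICC of 0.02 to 0.05. With 32 schools it is about 6% to 8%. The direction is certain if the ICC is above zero; the size is not known, because the ICC and the number of schools are not stated.

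The problem would grow if the screened sample were analysed: with 975 pupils in 8 schools, the simulated error for a school-level factor is 20% to 47% at ICC 0.02 to 0.10. The article does not say that it will be.

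The efficacy conclusions do not depend on this point. Severity is low.

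**What to change.** In section 2.9.4:
- State whether the analysis uses the randomised pupils or the screened sample.
- Fit the logistic regression with a random intercept for school, or with cluster-robust standard errors and a small-cluster correction. The correction matters with about 8 schools, where a two-level school factor has roughly 8 − 2 = 6 degrees of freedom.
- Replace the screening t-tests and chi-square tests by single-factor versions of the same model, so that clustering is respected before variables are selected.

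Apply the same variance method to any confidence interval reported for overall depression incidence.

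Adding school to the PSQI and BDI models is optional: it would reduce the standard error of the arm contrast by about 0.5% to 2.6% and is not needed for validity.

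The cost is analysis wording only. Section 2.2 already has school attributes recorded, and recruitment, sample size and conduct do not change. The price is wider intervals for school-level factors, and with few schools little power to detect them.

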#### Inclusion criteria

2.2.1

(1) The diagnosis met ICSD-3 criteria, characterized by difficulty initiating sleep (>20 minutes), difficulty maintaining sleep, or early morning awakening despite adequate sleep opportunity, accompanied by daytime functional impairment. These symptoms occurred at least three times per week and persisted for more than three months.(2) Age between 13–18 years;(3) PSQI score > 7;(4) No psychiatric medication treatment;(5) No communication or cognitive impairments;(6) Signed informed consent.

#### Exclusion criteria

2.2.2

(1) Sleep disorders caused by organic diseases such as epilepsy, stroke, etc.;(2) Sleep disorders caused by schizophrenia or other severe psychiatric disorders;(3) Diagnoses of other sleep disorders, such as obstructive sleep apnea, REM sleep behavior disorder, or restless legs syndrome;(4) Received AA therapy for insomnia in the past month;(5) Alcohol and/or other drug abuse or dependence.

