### Blinding

2.6

To further improve the effectiveness of the blind method, participants in both the AA group and the SAA group were uniformly informed that they needed to apply pressure after applying the skin-colored tape, thereby reducing patients’ sensitivity to group differences. Additionally, the skin-colored tape used in both the AA and SAA groups was identical in appearance and texture, and was fixed by researchers at the same ear acupoint locations, ensuring that they could not be distinguished visually. Participants, evaluators, and statisticians will remain blinded throughout the study to minimize potential bias arising from procedural differences. As acupuncturists are responsible for delivering the AA and SAA interventions, they cannot be blinded to group allocation; however, they will not participate in outcome assessments. Evaluators will remain fully blinded to group assignments. They will solely be responsible for data collection and are prohibited from discussing treatment-related information with participants.

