#### AA group

2.7.2

In the AA group, AA will be applied in addition to sleep hygiene education. Points: Shenmen (TF4, located in the triangular fossa, above the division of the ear lobe), Subcortex (AT4, on the inner side of the ear), Endocrine (CO18, anterior lower part of the ear canal), Liver (CO12, behind the lower part of the ear), Heart (CO15, central part of the ear), Kidney (CO10, below the upper and lower branches of the ear lobe) (**Figure 3**). These points will be carefully located according to the guidelines in the “Illustrated Ear Acupuncture” by Shanghai Science and Technology Publishing House. After evaluation, the most sensitive areas will be treated with ear acupressure beans. Each session will treat one ear, with changes to the other ear every 3 days. Patients will be instructed to press the acupressure beans 3–5 times per day, 1–2 minutes per session. The treatment will last for 8 weeks, followed by follow-ups at 3 months and 6 months.

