#### SAA group

2.7.3

In the SAA group, SAA will be applied in addition to sleep hygiene education. The same points as in the AA group will be selected, but adhesive tapes without seeds will be placed on the ear. To reduce intergroup differences and improve the effectiveness of the blinded method, the SAA group will also be required to press the ear patches according to uniform instructions to maintain consistency with the AA group’s operating procedures. This will prevent patients from easily guessing the groupings and ensure similarity in the operating experience between the two groups during the intervention. At the end of the study, patients will receive the same AA treatment as the ear acupressure group.

In addition, to minimize dropout rates and enhance participant adherence, researchers will engage with participants during each replacement of the ear acupressure beans. Participants will be reminded to apply pressure according to the prescribed frequency and duration, and to regularly monitor the placement and condition of the ear acupressure beans. These measures aim to encourage continued compliance with the study protocol.

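### Exclusion 4 bars auricular acupressure (AA) only when given for insomnia in the past month, so pupils using AA for another indication, or who know how a bead feels, can be randomised to seed-free sham or control

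*Protocol article*

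**What the plan says.** Section 2.2.2 (Exclusion criteria), item 4, excludes pupils who "Received AA therapy for insomnia in the past month". No inclusion criterion in section 2.2.1 requires pupils to be new to AA. The item there on psychiatric treatment concerns medication. The Introduction describes AA as "widely used for treating insomnia and depression".

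In section 2.7.3 the sham uses the same points as the active arm, but "adhesive tapes without seeds will be placed on the ear", and "the SAA group will also be required to press the ear patches according to uniform instructions". Section 2.7.2 tells AA pupils to "press the acupressure beans 3–5 times per day, 1–2 minutes per session". Section 2.6 (Blinding) says the tapes match in appearance and texture, "ensuring that they could not be distinguished visually", and states that "Participants, evaluators, and statisticians will remain blinded throughout the study".

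Allocation is 1:1:1 (section 2.5). PSQI and BDI are the primary outcomes (section 2.8.1), and the Discussion lists reliance on self-report among the limitations.

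**The concern.** Exclusion 4 applies only if the AA was for insomnia and was given within the last month. AA for any other reason is allowed, even if it is still going on. So is AA for insomnia that ended more than a month ago. This matters in two ways.

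- **Concurrent or recent AA for another indication.** The protocol itself names depression as a common use of AA, and BDI is a co-primary outcome. A pupil using AA for low mood can be randomised to SAA or control and so bring the active treatment into a comparison arm.
- **Recognition of the sham.** The two devices differ by the seed, and the pupil presses on the spot where the seed would be. The assurance in section 2.6 is visual. A pupil who has worn beads is more likely than a naive pupil to notice that the seed is missing, or that it is present.

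Controls receive sleep hygiene education without tape (section 2.7.1), so AA against SAA is the only contrast in which participants can be masked. Both primary outcomes are self-reported and therefore open to expectation.

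**Working it through.** The plan states no figure on this point, so there is nothing to reproduce. The check has two parts.

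**1. Who passes exclusion 4**

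| Earlier AA | For insomnia? | Within one month? | Excluded? |
|---|---|---|---|
| For insomnia, two weeks ago | yes | yes | yes |
| For insomnia, five weeks ago | yes | no | no |
| For low mood, current | no | yes | no |
| For any other reason, last year | no | no | no |

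Three of the four kinds of pupil are eligible and can be allocated to any arm.

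**2. Illustrative size**

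Inputs from section 2.3 of the protocol: 65 randomised per arm (52 after 20% dropout), planned PSQI change 2.63, SD 3.32.

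Assumed inputs, not in the documents: a share p = 5–20% of enrolled pupils with any earlier AA, and a mean PSQI shift b = 1–2 points in a pupil who recognises the allocation.

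- Exposed pupils per arm = 65 × p: 65 × 0.05 = 3.25 and 65 × 0.20 = 13.
- Chance of at least one in SAA = 1 − (1 − p)^65. At p = 5% this is 1 − 0.95^65 = 0.96.
- Shift in the AA–SAA contrast if one arm is affected = p × b: 0.05 × 1 = 0.05 and 0.20 × 2 = 0.40 points.
- As a share of the planned change: 0.05 / 2.63 = 1.9% and 0.40 / 2.63 = 15%.
- If both arms shift in opposite directions, these double to 0.10–0.80 points. The upper end is 0.80 / 2.63 = 30%.

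Concurrent AA acts the other way. As an upper bound, suppose every exposed SAA pupil is a current user with the full 2.63-point benefit. The contrast then shrinks by p × 2.63: 0.05 × 2.63 = 0.13 and 0.20 × 2.63 = 0.53 points. Two-sided 5% power for a simple two-group comparison with 52 per arm is about 0.98 at 2.63 / 3.32 = 0.79 SD. It falls to about 0.97 and 0.90 under these two dilutions. Loss of power is therefore not the main issue. The main issue is what the AA–SAA estimate means.

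The two mechanisms have opposite signs, and the documents give no basis for weighing one against the other.

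**The case against.** The strongest reply is that the weakness lies in the sham and not in eligibility. A naive SAA pupil may also notice that there is nothing under the tape, and pupils sampled by class can compare ears. Rewording exclusion 4 changes none of that. This is correct and limits what the fix can achieve. It does not justify a rule that also admits the pupils best placed to recognise the difference.

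Second, no exposure rate for Nanjing pupils is given. The Introduction's remark on wide use is general, and the Abstract says AA research has mostly been in adults. This also stands: 5–20% is only an assumption, and at its lower end the effect is negligible.

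Third, concurrent AA is a concomitant-treatment matter that a full protocol may cover. If it does, the first mechanism narrows to recent use and the recognition point is unchanged. What the article states is an exclusion limited by indication, and nothing in it explains that limit.

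A reader might also infer that the one-month window contradicts a trial in which "follow-up will be conducted at 3 months and 6 months post-treatment", so that carry-over contaminates baseline. The documents do not support this. The follow-up is there to evaluate whether effects last, which does not assert that they do, and section 2.2.2 does not describe the month as a washout. Entry also requires symptoms lasting over three months and PSQI above 7 (section 2.2.1). A pupil with a large residual benefit from a completed course is therefore unlikely to qualify, and randomisation balances past courses across arms in expectation.

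**Conclusion.** The point holds in a limited form. Exclusion 4 as worded admits pupils with current or recent AA for another indication to SAA and control. It also admits bead-experienced pupils to the only contrast in which participants can be masked, with self-reported primary outcomes. Under assumed exposure of 5–20% and a recognition shift of 1–2 PSQI points, the AA–SAA contrast moves by 0.05–0.4 points if one arm is affected. It moves by up to 0.8 if both are, against the planned 2.63. Concurrent AA would pull it back.

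Two stronger conclusions may be tempting and should not be drawn. One is that the trial is biased in favour of AA: the mechanisms oppose each other and the net sign is unknown. The other is that any experienced pupil will certainly identify the sham: the documents contain no evidence on this, and a raised chance of recognition is all the argument needs. Carry-over from a completed course is minor. Severity is low to moderate.

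**What to change.** Remove both limits from exclusion 4, so that it reads: *any previous auricular acupressure or other auricular therapy, for any indication*. Add one screening question to support it.

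If lifetime naivety is judged too strict, or recruitment is already under way, the minimum is to:

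- remove the indication limit;
- record any earlier AA (indication and date) before randomisation;
- run a sensitivity analysis of PSQI and BDI in AA-naive pupils.

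Because naivety is a baseline characteristic, that subset keeps the randomised comparison. If 5–20% are exposed, its standard error is larger by a factor of √(1/0.95) = 1.03 to √(1/0.80) = 1.12.

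Lengthening the window to six months would not be enough alone. A pupil who wore beads seven months ago may still know how they feel.

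**Cost.** Some otherwise eligible pupils are lost, and the sample must be described as AA-naive. On the same assumption, filling 195 places needs 195 / 0.95 ≈ 205 to 195 / 0.80 ≈ 244 otherwise eligible pupils, which is about 10 to 49 more. The sampled population rises from 975 to 975 / 0.95 ≈ 1,026 or 975 / 0.80 ≈ 1,219. The cost is substantial only where exposure is common, which is also where the problem is largest. The criterion depends on recall, and it does not cure the difference in feel between tape and bead for naive pupils.
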